## Abstract

**Background:**

Hwabyung is a Korean culture-bound syndrome characterized by anger-related physical and psychological symptoms. Depressive disorder is a common mental illness occurring worldwide, and has been reported to have a high comorbidity rate with Hwabyung. For patients with depressive disorders, differential diagnosis and combined treatment for Hwabyung should be considered. Mindfulness and Qigong may be effective alternatives for regulating emotions such as depression, anxiety, and anger. This study aims to investigate whether Mindfulness and Qigong Training for Self-Healing (MQT-SH) would improve emotional problems in patients with Hwabyung and depressive disorder.

**Methods:**

This study will be a two-arm block randomized controlled trial. A total of 64 participants will be recruited and randomly assigned to either experimental or control group. While the experimental group will perform MQT-SH for the first six weeks, the control group will receive no treatment. During the next six weeks, the control group will perform MQT-SH for ethical equity. Assessments will be conducted at baseline, post-intervention (6 weeks) and follow-up (12 weeks). The primary outcomes would be Hwabyung and depression, while the secondary outcomes would include anxiety, anger, and vitality.

**Discussion:**

This study will provide a basis for assessing the effectiveness of mindfulness and Qigong training in patients with Hwabyung and depressive disorder.

**Ethics and dissemination:**

This study was approved by the Institutional Review Board of Kyung-Hee University Oriental Medicine Hospital in Gangdong (KHNMCOH 2023-09-003). The results will be disseminated through peer-reviewed publications.

**Trial registration:**

This trial was registered with the Clinical Research Information Service (CRIS), Republic of Korea, No. KCT0008937 and was registered on November 10, 2023.

## Introduction

1

Hwabyung is a disorder that is culturally specific to Korea (1). It is a syndrome in which negative emotions such as anger cannot be resolved and explode. According to previous research, physical symptoms include chest stuffiness, heat, feeling of something pushing up, and the feeling of a lump in the throat or pit of the stomach (2). Psychological symptoms include feelings of unfairness, resentment, and anger (2). Symptoms have been reported to be associated with specific stressful events (3). Research on the diagnosis of Hwabyung commenced in the 2000s, and the diagnostic criteria were first established by Kim et al. (2). When standardized diagnostic criteria are applied, the prevalence of Hwabyung in Koreans has been reported to range between 4.2-13.3% (4–7). Treatment for Hwabyung is generally provided by Korean medicine doctors (3).

In Korean medicine, it is believed that Hwabyung manifests as a result of problems with the circulation and regulation of ‘Qi.’ According to Donguibogam, a classic in Korean medicine literature, physical and psychological problems occur when Qi is not properly circulated (通卽不痛 不通卽痛) (8). Hwabyung is understood as a state of psychological blockage caused by persistent unresolved resentment in which the emotion of anger is biased upward and, as a consequence, Qi cannot circulate properly (9). To treat these symptoms, Korean medicine aims to achieve balance and harmony between the mind and body through the optimal circulation of Qi.

Depression is a mental health problem characterized by absence of positive emotions such as interest and pleasure, and a depressed mood (10). It is a mental illness that not only negatively affects an individual's quality of life, but also their overall occupational and social functioning (11). Depressive disorder is a common disease occurring worldwide. More than 185 million people were diagnosed with depression in 2019, and its prevalence is reportedly higher among women (3.07%) than men (1.89%) (12). In the 2019 Global Burden of Disease Study, the disease burden of depressive disorder ranked 13th among the top 25 diseases, showing a disease burden similar to that of AIDS, cirrhosis, lung cancer, and headache (13). In particular, it can be said that symptoms of depression have become more serious due to the recent impact of COVID-19 (14).

Hwabyung and depressive disorder have a high comorbidity rate. Epidemiological surveys have shown that 44% of the patients with Hwabyung have depressive disorder (15). Considering the fact that previous research (16) has demonstrated that 28.5% of patients with depressive disorder have generalized anxiety disorder as a comorbidity, it can be considered that Hwabyung and depressive disorder have a very high comorbidity rate. Therefore, in patients with depressive disorder, differential diagnosis and combined treatment for Hwabyung should be considered.

Recently, various mind-body interventions, such as mindfulness and Qigong, have been proposed as alternatives for treating mental disorders while minimizing the side effects of drugs. Mindfulness, which based on traditional Buddhist practices, is operationally defined as “paying attention in a particular way: on purpose, in the present moment, and nonjudgmentally” (17). Mindfulness, a non-judgmental concentration on the present moment, results in a relaxation response associated with activation of the parasympathetic nervous system (18). Mindfulness helps patients with depression or Hwabyung stay in the present moment and not trapped in negative thoughts or past resentment (19, 20). Based on these principles of mindfulness, a standardized program has been developed for emotional regulation, including stress reduction and prevention of depressive relapse (19, 21). In fact, mindfulness-based programs have been shown to improve depression in patients with depressive disorders and university students (22, 23), as well as Hwabyung in middle-aged females (20).

Qigong, which has its basis in the Taoist tradition, is a system of practices intended to cultivate control over life energy, known as Qi, through various body postures and movements, deep breathing, and mental concentration (24). Qigong is a broad concept that includes both static and movement-based practices, and is classified into various methods depending on tradition, such as Ba Duan Jin, Liu Zi Jue, Wu Qin Xi, and Kouksundo (25). The broad concept of Qigong and its diverse methods make it difficult to standardize programs. To compensate for these limitations and increase reproducibility in follow-up studies, this study defined Qigong operationally as feeling, accumulating, and utilizing Qi. Previous studies have shown that Qigong improves depression and Hwabyung (26, 27). The effects of Qigong on emotional regulation are explained by mindfulness. Qigong, along with Tai Chi and yoga, is referred to as meditative or mindful movement (28, 29), and is considered to share the therapeutic mechanisms of mindfulness meditation for emotional regulation (30). From a Korean medicine perspective, Qigong is believed to ameliorate Hwabyung and depression through the regulation of Qi (8, 9).

This study aims to investigate the effectiveness of Mindfulness and Qigong Training for Self-Healing (MQT-SH) from the comorbidity of depression and Hwabyung. The MQT-SH is a standardized Korean medicine mind-body intervention that aims to achieve a healthy balance between the mind and body (9). The primary hypothesis is that MQT-SH significantly reduces Hwabyung and depression in comparison to the control group. The secondary hypothesis is that MQT-SH reduces anxiety and anger while increasing vitality compared to the control group.

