### Sample size

2.5

The sample size was estimated using G*power (37). The sample size calculation is based on a power of 80% and a type I error of 5%, as well as a moderate effect size for the intervention (partial *η*^2^ = 0.04). A minimum sample size of 25 participants per group is estimated (50 participants in total). This number was obtained by performing a simulation procedure using repeated-measures ANOVA, considering the existence of a significant 2 (group: experimental *vs*. control) × 2 (time: T1 *vs*. T2) interaction effect. Considering a dropout rate of 20%, we aim to include 32 participants per group (64 participants in total).

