#### Hwabyung scale

2.9.1

The Hwabyung scale (40) will be used to assess Hwabyung-related personality and symptoms. This scale comprises 16 items on Hwabyung personality and 15 items on Hwabyung symptoms. This is a self-reported 5-point Likert scale. The total score ranges from 0 to 64 for Hwabyung personality, and from 0 to 60 for Hwabyung symptoms. Higher scores indicate higher Hwabyung personality and symptoms. In a previous study (40), the Cronbach's alpha for the Hwabyung scale was .85 for Hwabyung personality, .93 for Hwabyung symptoms, and .93 overall.

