#### Hwabyung comprehensive test

2.9.2

The Hwabyung Comprehensive Test (41) will be used to assess Hwabyung-related symptoms and psychological characteristics. This test consists of 13 items on Hwabyung symptoms, 5 items on the incident questionnaire, and 21 items on Hwabyung psychological characteristics. Hwabyung symptoms and psychological characteristics will be used to interpret scores. This test is a self-reported 5-point Likert scale. The total score ranges from 0 to 52 for Hwabyung symptoms, and from 0 to 84 for Hwabyung psychological characteristics. Higher score indicates more severe Hwabyung symptoms and vulnerability. In a previous study (41), the Cronbach's alpha for the Hwabyung Comprehensive Test was .89 for Hwabyung symptoms and .95 for Hwabyung psychological characteristics.

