#### Hamilton depression rating scale

2.9.3

In this study, a structured interview manual will be used to increase inter-rater reliability.

The Korean version of the Hamilton Depression Rating Scale (42) will be used to assess depression. This is an observer rating scale consisting of 17 items. Each item is scored from 0 to 2 or from 0 to 4. The total score ranges from 0 to 52. Higher scores indicate more depressive symptoms. In this study, a structured interview manual will be used to increase the inter-rater reliability (39).

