## Discussion

3

The purpose of this study is to investigate the effectiveness of a mindfulness and Qigong program for patients with depression and Hwabyung. This study is designed as a two-armed block randomized controlled trial. This study will primarily investigate the effectiveness of MQT-SH on Hwabyung, depression, anxiety, anger, and vitality. Additionally, this study will investigate the follow-up effect of MQT-SH and perform a subgroup analysis to compare the differences in the effect according to the amount of home training.

While depression is characterized by a sad mood or absence of joy or interest (10), Hwabyung is characterized by a combination of physical (chest tightness, heat, etc.) and psychological (resentment, resentment, etc.) symptoms related to anger (2). Although depression and Hwabyung have different diagnostic criteria, they have a high likelihood of comorbidity (15). In fact, 44.1% of patients with Hwabyung were diagnosed with depressive disorder, and 18.3% were diagnosed with both depressive and anxiety disorders (45). This suggests that Hwabyung is not only related to depression, but also to anxiety. Therefore, interventions are needed to comprehensively deal with various emotional problems such as depression, anxiety, and anger.

Mindfulness and Qigong can be used as transdiagnostic approaches for improving emotion regulation. Previous studies have shown that mind-body interventions, such as mindfulness and Qigong, improve depression, anxiety, and anger (27, 46–48). Mindfulness is a basic factor in several mind-body interventions and is considered a Qigong therapeutic mechanism for emotional regulation (20). This study investigates whether mindfulness and Qigong interventions improve emotional regulation in patients with Hwabyung and depressive disorder. MQT-SH is a standardized mind-body intervention that combines mindfulness and Qigong (9). This study adhered to the standard procedure of MQT-SH, but made some modifications to the period and content in consideration of the study setting and participants.

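### Several primary scores but a sample size for one test: whichever success rule is meant, either the stated 5% type I error or the stated 80% power fails

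*Protocol article*

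**What the plan says.** The primary hypothesis in the Introduction covers two constructs joined by 'and': "The primary hypothesis is that MQT-SH significantly reduces Hwabyung and depression in comparison to the control group". The Abstract gives the same split: "The primary outcomes would be Hwabyung and depression, while the secondary outcomes would include anxiety, anger, and vitality".

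Section 2.9 then lists three primary instruments.

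- **Hwabyung Scale (2.9.1):** "This scale comprises 16 items on Hwabyung personality and 15 items on Hwabyung symptoms", each with its own range: "The total score ranges from 0 to 64 for Hwabyung personality, and from 0 to 60 for Hwabyung symptoms".
- **Hwabyung Comprehensive Test (2.9.2):** "The total score ranges from 0 to 52 for Hwabyung symptoms, and from 0 to 84 for Hwabyung psychological characteristics".
- **HDRS (2.9.3):** "The Korean version of the Hamilton Depression Rating Scale (42) will be used to assess depression", with one total from 0 to 52.

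Hwabyung therefore has four described scores, two of them symptom scores, and depression has one.

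Section 2.5 is "based on a power of 80% and a type I error of 5" per cent, with partial eta squared 0.04, for one 2 × 2 interaction. It arrives at 25 per group and enrols 32 per group to allow for 20% dropout. Section 2.13 specifies a 2 × 2 repeated-measures ANOVA on T1 and T2. It names no score, gives no significance level per test and does not say how several primary results combine.

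**The concern.** A trial with several primary scores needs a rule for what counts as success, and that rule determines which error rate and which power apply. If one significant score is enough, the chance of a false claim rises with the number of scores. If all must be significant, the chance of a true claim falls. The sample size section takes neither into account: it gives one test the full 5%.

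The practical risk lies mainly with Hwabyung. Without a deciding score, a claim could rest on whichever of four scores is significant, including the personality score. Recruitment has already started (section 3.3), so the rule should be settled before outcomes are analysed.

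**Working it through.** **Inputs from the article.** Partial eta squared 0.04, alpha 0.05, power 80%, 25 per group evaluable (N = 50), 20% dropout, 32 per group enrolled (section 2.5); three primary instruments with five described scores (section 2.9).

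**Assumptions.** The T1–T2 correlation rho is not given; 0.5 is used, the G*Power default. Correlations between the change scores are not given either; equal correlations of 0.3 to 0.7 are shown, with independence as the limit.

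**Step 1: reproduce the plan's figure.** f² = 0.04/0.96 = 0.04167. For the within-between interaction with m = 2 time points, λ = f²·N·m/(1 − rho) = 0.04167 × 50 × 2/0.5 = 8.33, with 1 and 48 degrees of freedom. Power at alpha 0.05 is 80.7%, and N = 50 is the smallest even total reaching 80%. Dropout: 25/(1 − 0.20) = 31.25, rounded up to 32 per group. The stated numbers are reproduced as a calculation for one score at the full 5%.

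**Step 2: any score may count, each tested at 5%.** With k independent scores and no true effect, the chance of at least one significant result is 1 − 0.95^k. For k = 3 this is 14.3% and for k = 5 it is 22.6%. Correlated change scores (25 per arm) were simulated; the results are in the table.

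**Step 3: HDRS plus any one of the four Hwabyung scores.** Suppose depression truly improves and Hwabyung does not. The false Hwabyung claim then depends on the four null scores: 1 − 0.95^4 = 18.5% if independent, and about 13–17% at correlations 0.7 to 0.3. These are limits approached as the power on HDRS nears 1. With HDRS at the planned 80.7% and independent scores, the error is 0.807 × 0.185 = 15%.

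**Step 4: all scores must succeed, each tested at 5%.** The type I error stays at or below 5%. Joint power with independent scores is 0.807^k, which is 52.6% for k = 3 and 34.3% for k = 5.

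| Correlation between scores | Any counts: error, 3 tests | Any counts: error, 5 tests | All must win: power, 3 tests | All must win: power, 5 tests |
|---|---|---|---|---|
| 0 (formula) | 14.3% | 22.6% | 52.6% | 34.3% |
| 0.3 | 13.6% | 20.8% | 58.1% | 44.7% |
| 0.5 | 12.4% | 18.6% | 62.4% | 52.4% |
| 0.7 | 11.1% | 15.1% | 66.9% | 60.1% |

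**Step 5: the reduced set, one Hwabyung score and HDRS, at 50 evaluable.**

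- Both must be significant at 5%: joint power is 67.7% at correlation 0.3 and 72.4% at 0.7.
- Either may be claimed: at alpha 0.025 with λ = 8.33, power per score is 71.5%. This is the Bonferroni value and the lower bound for Holm. Under Holm, power per score is about 77% if both effects are as planned.

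**The case against.** **The rule may be in an analysis plan that is not shown.** A success rule and a multiplicity method are commonly left to that document, and their absence from an article is not an error in itself. This stands. However, the article itself fixes a primary set of several scores and a sample size for one test at full alpha. On the stated assumptions, no rule over several primary scores gives both 5% and 80% at 50 evaluable. Naming one deciding score would, but that changes what section 2.9 lists as primary.

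**A reader might infer that the 5% error is simply not held.** The article does not support that. The 5% appears only in section 2.5, so testing each score at 5% is an inference. The hypothesis says 'and'; if every score must be significant, 5% is held without adjustment and the loss is in power alone. The 'and' does not settle the matter, though, because it does not say how many of the four Hwabyung scores are needed (step 3).

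**A reader might take five confirmatory tests and 22.6% as established.** Section 2.9 designates three instruments. It describes subscale ranges without saying that each subscale is tested separately, and it also reports an overall reliability for the Hwabyung Scale. Independence is implausible for related questionnaires. The correlated ranges are the fairer figures, for three tests as well as five.

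**A reader might see a wider primary set in the Discussion**, which says "This study will primarily investigate the effectiveness of MQT-SH on Hwabyung, depression, anxiety, anger, and vitality". The Abstract, the Introduction and section 2.10 consistently make anxiety, anger and vitality secondary. The sentence is loose wording and adds nothing to this point.

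**Conclusion.** The point holds in conditional form: the article states 5% and 80% for one interaction but lists several primary scores, and one of the two figures fails under either success rule. If any score may count, family-wise error is about 11–14% for three tests or 15–21% for five. If HDRS plus any one Hwabyung score suffices, the error can approach 13–18.5% when only depression improves. If all must succeed, 5% is held and joint power is about 58–67% for three or 45–60% for five.

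These sizes rest on rho 0.5, which reproduces the plan's N, on equal correlations of 0.3 to 0.7 between scores (the 18.5% is the independent limit), and, for power, on the planned effect applying to every score. That a mismatch exists does not depend on the exact correlations; its size does. It should be fixed, because what the trial may conclude about Hwabyung depends on it.

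**What to change.** Before outcome data are analysed:

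1. **Section 2.9.** The sponsor names one deciding Hwabyung score and the HDRS total as the primary outcomes and moves the other Hwabyung scores to secondary. The article gives no statistical ground for preferring one Hwabyung score; the choice is the sponsor's, and what matters is that it is made in advance.
2. **Section 2.13.** State one rule. Either both scores must be significant at 5%, which matches the 'and' in the hypothesis, or either may be claimed using Holm at an overall 5%. If Holm is chosen, reword the hypothesis so that it no longer reads as requiring both.
3. **Section 2.5.** Restate power to match. If both are required, joint power is about 68–72% at 50 evaluable. Under Holm, power is at least 71.5% per score, and about 77% if both effects are as planned. State the assumed rho and the correlation between the scores.

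The figure of 83% per score at alpha 0.025 with 32 per arm should not be quoted. It assumes no dropout, whereas section 2.5 expects 20% and section 2.8 says that dropouts are not assessed further.

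The cost is a change of wording and a somewhat less favourable stated power. No new data or participants are needed.

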## Methods

2

### Trial design

2.1

This study is designed as a two-arm block randomized controlled trial. Patients will be assigned to either the experimental or the control group. The trial will be conducted for a duration of 12 weeks. During the first six weeks, the experimental group will receive MQT-SH, while the control group will receive no treatment as a waiting list control (WLC). During the next six weeks, the control group will receive MQT-SH with consideration for ethical equity. Assessments will be performed at three points: baseline (T1), post-intervention (T2; 6 weeks), and follow-up (T3; 12 weeks).

This trial was registered with the Clinical Research Information Service (CRIS), Republic of Korea (KCT0008937). This trial complies with the SPIRIT guidelines and will be conducted in accordance with the tenets of Declaration of Helsinki. **Figure 1** presents a flow chart representing the overview of the study design.

**Figure 1 f1:**
[figure not shown]
Study flow chart.

### Study setting

2.2

This trial will be conducted at Kyung Hee University Korean Medicine Hospital in Gangdong, South Korea. Participants will be recruited through advertisements in hospital and subways. Potential participants interested in participating will be informed about the study. If they agree to participate, they will be screened to assess the inclusion and exclusion criteria.

### Eligibility criteria

2.3

Participants will be included if they i) have simultaneously been diagnosed with Hwabyung and depressive disorder by the Hwa-Byung Diagnostic Interview Schedule (HBDIS) (2) and Structured Clinical Interview for DSM-5 (SCID-5) (31); ii) are ≥ 19 years of age; and iii) can participate in the study by considering the timetable.

### Interventions

2.4

Participants will be randomly assigned to either MQT-SH or WLC.

#### Mindfulness and Qigong training for self-healing

2.4.1

The experimental group will perform MQT-SH for the first six weeks. MQT-SH is a standardized mindfulness- and Qigong-based program to enhance self-healing (9). The goal of MQT-SH is to achieve optimal physical and psychological conditions. To achieve this goal, MQT-SH consists of two modules: i) balance and harmony, and ii) circulation and interchange. According to the traditional Oriental medicine, excessive emotions cause physical and psychological problems (32), and these imbalanced problems can be solved through circulation and interchange of energy (33). Balance and harmony have recently become the core principles of health and well-being across various cultures (34–36).

The balance and harmony module consists of the 1st to 3rd sessions. This module emphasizes the balance of inhalation/exhalation, sympathetic/parasympathetic nervous systems, and past/future/present for health. This module teaches various mindfulness-based training for healthy balance. In the first session, the participants will be taught the meaning of breathing and how to use it. Subsequently, breathing meditation will be performed. Breathing meditation involves counting numbers or adding words while concentrating on breathing. In the second session, participants will be educated about the balance and harmony of stress and relaxation. After educating the patients, body scan and autogenic training will be performed. In the third session, the participants would be educated on the meaning of mindfulness, and sitting meditation will be performed subsequently. Sitting meditation focuses on the awareness of breathing and bodily sensations.

The circulation and interchange module consists of the 4th to 6th sessions. This module teaches Qigong to encourage proper circulation and interchange of Qi. In MQT-SH, Qigong is operationally defined in three ways: feeling, accumulating, and utilizing Qi. In the fourth session, participants will be educated about the energy that could be experienced phenomenologically, and after education, meditation with Qi will be performed. The goal of meditating with Qi is to sensuously experience Qi in a comfortable and calm state. Meditation with Qi consists of breathing meditation, body scan, and mindfulness of the energy called Qi. In the fifth session, two ways of obtaining energy (e.g., breathing and eating) would be taught to the participants. Moreover, Danjeon breathing and eating meditations will be performed. In the sixth session, participants will be taught to use energy, and simple Qigong movements and walking meditation will be performed. **Table 1** provides the detailed structure by session.

**Table 1 T1:** Sessions of the intervention.

Module	Session	Subject	Education (20 min)	Practice (40 min)	Group activities (30 min)
Balance and harmony	1	Breathing	Understanding breathing; How to use breathing	Breathing meditation	1) Sharing experiences 2) Question and answer
	2	Relaxation	Balance and harmony of stress and relaxation	Autogenic training; Body scan	1) Checking home training 2) Sharing experiences 3) Question and answer
	3	Mindfulness	Understanding mindfulness	Sitting meditation (breathing and bodily sensations)	
Circulation and interchange	4	Feeling Qi	Energy that can be experienced phenomenologically	Meditation with Qi 1) Breathing meditation 2) Body scan 3) Mindfulness of Qi	1) Checking home training 2) Sharing experiences 3) Question and answer
	5	Accumulating Qi	Two ways to obtain energy (e.g. breathing and eating)	Danjeon breathing; Eating meditation	
	6	Utilizing Qi	How to use energy	Qigong movements; Walking meditation	

The MQT-SH period may vary depending on the setting (9). A manual for researchers and participants was developed to improve compliance to the intervention protocol. In this study, the MQT-SH will be conducted once a week for 1.5 h for a total of six weeks. Each session will consist of 20 min of education, 40 min of practice (i.e., meditation), and 30 min of group activities, such as checking home training and sharing practice experiences. This intervention will be conducted as a group program, with a maximum of 12 people per group. Participants will be asked to perform home training five times a week for at least 30 min each day. Participants will receive guided audio materials for home training. Dropouts will be defined as i) individuals attending three or less out of six sessions, ii) those who complain of physical or psychological discomfort and want to give up because of such discomfort, or iii) those who would want to give up for reasons other than discomfort.

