#### Wait-list control

2.4.2

The control group will be assigned to WLC and will receive no treatment for the first six weeks. Considering ethical equity, the control group will undergo the same MQT-SH over the next six weeks.

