### Statistical analyses

2.13

Analyses based on the Intention-To-Treat (ITT) principle will be conducted, with missing data imputed using expectation-maximization (EM) algorithm.

To investigate the effect of MQT-SH, 2 (group: MQT-SH *vs*. WLC) × 2 (time: T1 *vs*. T2) repeated measures ANOVA will be performed. If the interaction between the group and time is significant, a simple main effect analysis will be performed.

Additional analyses will be performed. First, to investigate the follow-up effect of the MQT-SH, a paired t-test will be performed to compare T3 and T1 and T3 and T2 in the experimental group alone. Second, a paired t-test comparing T3 and T2 in the control group will be performed to investigate the effects of MQT-SH. Third, a subgroup analysis will be performed to investigate the difference in effectiveness depending on the amount of home training. For this purpose, 2 (amount: top 30% *vs*. bottom 30%) × 2 (time: pre-intervention *vs*. post-intervention) repeated-measures ANOVA will be performed. Data from both the experimental and control groups will be used for subgroup analysis.

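### MQT-SH is taught in classes, but the sample size and main ANOVA treat participants as independent, so the standard error is too small if class-mates' changes are positively correlated

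*Protocol article*

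**What the plan says.** Section 2.4.1 of the protocol article describes six weekly sessions of 1.5 hours: "This intervention will be conducted as a group program, with a maximum of 12 people per group". Each session includes "30 min of group activities, such as checking home training and sharing practice experiences".

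Section 2.4.2 describes the comparator: "The control group will be assigned to WLC and will receive no treatment for the first six weeks". Allocation is by individual, 1:1 (section 2.6).

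Section 2.5 gives the sample size: "A minimum sample size of 25 participants per group is estimated (50 participants in total"), raised to 32 per group for 20% dropout. On its source it says: "This number was obtained by performing a simulation procedure using repeated-measures ANOVA". The effect tested is the group-by-time interaction over T1 and T2.

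Section 2.13 fixes the main analysis as a group (MQT-SH, wait list) by time (T1, T2) design in which "repeated measures ANOVA will be performed. If the interaction between the group and time is significant, a simple main effect analysis will be performed". The Discussion confirms that the T1-T2 comparison of the two arms is the main one.

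Neither section has a class term, an ICC or a design effect. The limitations in 3.1 cover blinding and the single centre, not clustering.

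**The concern.** People taught together share sessions, discussion and peer influence, so their changes from T1 to T2 may be more alike than those of people in different classes. The planned ANOVA has no term for this. It would count 32 treated participants as 32 independent pieces of information, although they come from perhaps three classes.

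The wait-list arm has no classes before T2, so the design is partially nested: one arm is clustered and the other is not. With positive correlation, the standard error of the group-by-time effect is understated, confidence intervals are too narrow, and the test rejects a true null more often than 5%. At stake is how far a borderline primary result can be trusted.

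**Working it through.** **Inputs from the protocol article.** Class size at most 12 (2.4.1); no classes in the control arm before T2 (2.4.2); partial η² = 0.04, power 80%, α = 5%, 25 per arm before dropout and 32 after (2.5); 2 × 2 ANOVA (2.13).

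**Assumptions, not in the documents.** ICC of the T1-T2 change between 0.01 and 0.10. Three classes in the treated arm: 32/12 = 2.7, so three is the minimum. T1-T2 correlation 0.5, which is needed for the power figures only.

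**1. The plan's own figure.** f² = 0.04/0.96 = 0.0417. For the interaction with two time points, λ = f² × N × 2/(1 − 0.5). At N = 50, λ = 8.33 with (1, 48) df, and the noncentral F gives power 0.807. At N = 48 it gives 0.791. So 50 reproduces exactly under independence, with no hidden allowance for clustering. Dropout: 25/0.8 = 31.25, rounded up to 32 per arm.

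**2. Variance under partial nesting.** The 2 × 2 interaction test is a two-sample test on change scores. With class size m, the treated arm's variance is multiplied by 1 + (m − 1)ICC and the control arm's by 1. With equal arms, the average inflation is 1 + (m − 1)ICC/2.

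Example with 32 in three classes: m = 10.67. At ICC 0.05 the treated-arm factor is 1 + 9.67 × 0.05 = 1.483, the average is 1.242 and the standard-error ratio is √1.242 = 1.114.

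**3. Type I error of the planned ANOVA.** 2 × [1 − Φ(1.96/SE ratio)]. This needs no T1-T2 correlation.

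| ICC | SE ratio, 3 classes | Type I, 3 classes | Type I, 6 classes (m = 5.33) |
|---|---|---|---|
| 0.01 | 1.02 | 5.6% | 5.2% |
| 0.02 | 1.05 | 6.1% | 5.5% |
| 0.05 | 1.11 | 7.9% | 6.3% |
| 0.10 | 1.22 | 10.8% | 7.6% |

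Simulation of the planned test with classes of 11, 11 and 10 (100,000 runs) gives 5.5%, 6.1%, 7.9% and 10.8%.

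**4. Power.** The stated inputs with correlation 0.5 imply a standardized difference in change of d = √(4 × 0.0417 × 2/0.5) = 0.816. Two different tests must be kept apart.

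- *The planned ANOVA*, simulated with 25 per arm and classes of 9, 8 and 8, rejects 80.8% of the time at ICC 0 and 79.9%, 79.2% and 77.6% at ICC 0.02, 0.05 and 0.10. That is a loss of about 1 to 3 points.
- *A test using the correct standard error*, by normal approximation: power = Φ(d/SE − 1.96), with SE² = (2/n)[1 + (m − 1)ICC/2].

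| ICC | 25 per arm, 3 classes (m = 8.33) | 32 per arm, 3 classes (m = 10.67) |
|---|---|---|
| 0 | 82% | 90% |
| 0.02 | 80% | 88% |
| 0.05 | 76% | 83% |
| 0.10 | 70% | 76% |

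The approximation treats the ICC as known. A test that had to estimate it from three classes would do worse.

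**The case against.** **The ICC may be negligible.** The documents give none. The relevant ICC is that of the change, so stable class differences in baseline level cancel. The manual and guided audio (2.4.1) standardise delivery. At ICC 0.01 the error rate is about 5.5%, which matters little. This stands, and it is why the point is conditional.

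**Three classes is close to the worst case.** Twelve is a maximum, and smaller classes shrink the effect. This stands; the six-class column shows by how much.

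**A shared instructor is not an established source of correlation.** Section 3.1 refers to the instructor in the singular. One instructor for every class adds no variance between classes. This stands. Shared sessions and peer discussion remain as sources.

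**A reader might infer that the trial is underpowered on every outcome.** The documents do not support that. The larger losses belong to a corrected test, not to the planned ANOVA, so the inflated type I error and the larger power loss do not occur in the same test. If all 32 per arm complete, the corrected test still exceeds 80% at ICC 0.05. All power figures also depend on a correlation that section 2.5 does not state.

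**This could be left to an analysis plan.** The article does not leave the model open. It fixes a model that assumes independence, in both 2.5 and 2.13, alongside delivery in classes. That is more than an omitted detail.

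**Conclusion.** The concern holds in conditional form. The delivery in 2.4.1 and the independence assumed in 2.5 and 2.13 do not fit together, and if class-mates' changes are positively correlated the planned ANOVA overstates its precision. The firmer consequence is the error rate: about 6% to 11% against a nominal 5% for ICCs of 0.02 to 0.10 with three classes in an arm of 32, and less with more classes or a smaller ICC.

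The effect on power is secondary. It is slight for the planned test. For a corrected test it is about 3, 7 and 13 points at ICC 0.02, 0.05 and 0.10 with 25 analysed per arm. The ICC, the class count and (for power) the T1-T2 correlation are all assumptions, so these figures show a range of sensitivity and do not estimate this trial's actual error rate.

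**What to change.** 1. Record each participant's class.
2. In 2.13, report the primary group-by-time effect with its confidence interval and p-value, then repeat both with the MQT-SH arm's variance multiplied by 1 + (m − 1)ICC at fixed ICCs of 0.02, 0.05 and 0.10. For unequal classes take m as Σm²/Σm; for 11, 11 and 10 this is 342/32 = 10.7. Call the result robust only if it holds across that range.
3. In 2.5, state that the 80% assumes independent participants, and give the corrected-test power at the same ICCs together with the assumed T1-T2 correlation and class count.
4. In 3.1, list clustering by class as a limitation.

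A partially nested mixed model, with a random class effect in the MQT-SH arm only, may be added as supportive. It should not carry the conclusion, because about three classes estimate the class variance poorly.

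The cost is one recorded variable and some analysis wording. Section 3.3 says recruitment has started; none of this needs more participants or a change to the intervention. The downside is wider intervals and a slightly less favourable stated power.
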